### Main hypothesis

The use of Glubran 2® after AL in patients with BC can safely reduce the symptomatic seroma percentage.

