### Criteria for discontinuing or modifying allocated interventions {11b}

In accordance with the Declaration of Helsinki, participants can withdraw from the trial at any time and for any reason.

The withdrawal criteria is as follows: patients will be excluded from the study in any of the following scenarios: (a) the patient expresses their willingness to leave the study, (b) the patient is not able to accomplish the established clinical controls, (c) continuation of the study procedures may be detrimental to the patient’s health or well-being, (d) there is a concurrent illness that prevents compliance with patient monitoring and assessment procedures.

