### Main safety measures

The main safety measures are as follows: adverse events and post-surgical complications such as suture failure and surgical wound infection.

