## Statistical methods

### Statistical methods for primary and secondary outcomes {20a}

The statistical analysis plan (SAP) will be based on intention to treat principles in line with Consolidated Standards of Reporting Trials (CONSORT) guidelines.

Descriptive analysis of the study sample is as follows: as quantitative variables, the mean, median, range, and standard deviation will be analyzed. Absolute values and percentages will be used for qualitative variables. The frequency measures used will be prevalence, analysis of the homogeneity, or comparability of study groups. Quantitative variables will be assessed for normal distribution using the Kolmogorov–Smirnov or Shapiro–Wilk test.

Bivariate analysis of quantitative variables will be performed using Student’s *t*-test or Mann Whitney *U* test as appropriate.

For the analysis of qualitative variables, the chi square test or Fisher’s test will be used as appropriate. The OR (odds ratio) is considered as a measure of effect calculated by logistic regression.

In the multivariate survival analysis, the Cox regression method will be used, while for the multivariate analysis of risk factors, the logistic regression method will be used, introducing in the statistical model those variables that show statistical significance in the univariate analysis and/or those that in the bibliography and theoretical framework are prognostic factors.

Clinical lymphoedema-free survival will be analyzed using the Kaplan–Meier method, and survival curves will be compared using the Long-Range test and Cox regression. The safety analysis will be performed per protocol and will use the same statistical tests mentioned above. The level of significance is set at *p* < 0.05. The statistical analysis will be carried out with the Statistical Package for the Social Sciences (SPSS) version 21.

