### Methods in analysis to handle protocol non-adherence and any statistical methods to handle missing data {20c}

Patients who are included in the study but who do not meet the inclusion or exclusion criteria will be withdrawn from the analysis. Missing data will be excluded for the primary and secondary outcome analyses. Further analyses based on multiple imputation methods will be considered if appropriate. Analyses will be carried out based on the intention to treat principle.

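### Safety, one of two main objectives, is analysed per protocol with no analysis of all treated patients, so complication-related exclusions may understate the risk of the sealant

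*Protocol article*

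**What the plan says.** All references are to the protocol article.

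- **Main objectives** lists two aims: efficacy against symptomatic seroma, and safety and tolerability. The **Main hypothesis** joins them: the sealant "can safely reduce the symptomatic seroma percentage".
- **Main safety measures** are "adverse events and post-surgical complications such as suture failure and surgical wound infection".
- **Statistical methods {20a}** opens with intention to treat, then sets a different population for safety: "The safety analysis will be performed per protocol and will use the same statistical tests mentioned above". The per-protocol set is not defined.
- **Section {20c}** says "Analyses will be carried out based on the intention to treat principle". It also takes patients found not to meet the eligibility criteria out of the analysis.
- **Section {11b}** says "patients will be excluded from the study in any of the following scenarios". Besides the patient's own wish to leave (a) and inability to keep the planned visits (b), these include (c) "continuation of the study procedures may be detrimental to the patient’s health or well-being" and (d) "there is a concurrent illness that prevents compliance with patient monitoring and assessment procedures".
- **Intervention description {11a}** describes a single application of the sealant after the lymphadenectomy, before closure.
- **Section {18a}** requires a case report form for patients who do not finish follow-up, and **section {22}** requires all adverse events to be recorded, whether or not the surgery caused them.

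**The concern.** A per-protocol set has some purpose when a treatment is taken over time and one asks what happens in those who keep to it. Here nothing remains to adhere to after the operation. For the sealant, the patients a per-protocol set can still remove are those given the wrong allocation, those found ineligible, those who miss visits and those who leave. If sealant was applied, all of these were exposed to it.

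The reasons for leaving matter. Criterion (c) is about possible harm to the patient. Criteria (b) and (d) can follow from a complication, although they need not. Exclusion can therefore depend on the very outcome the safety analysis is meant to measure. A control patient who received sealant by mistake could also drop out of the comparison although exposed.

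At stake is the safety half of the main hypothesis. With few events expected in an arm of this size, the placing of two or three patients inside or outside the set can change the reported rate noticeably. Because the set is undefined, those decisions could be taken late. Sections {16c} and {19} show that the surgeon who enters the data knows the allocation.

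**Working it through.** **Inputs from the protocol article**

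- 67 patients per arm and 10% expected loss to follow-up (Sample size {14}).
- 25% against 7% symptomatic seroma, two-sided alpha 0.05, beta 0.2 (same section).
- Wound infection of 5–15% after lymphadenectomy (Background {6a}), used only to choose plausible event counts.

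**Reproducing the plan's own figure.** No number is given for safety, so the only figure to reproduce is the sample size. The formula is not stated; the arcsine formula is assumed.

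- h = 2·asin(√0.25) − 2·asin(√0.07) = 0.512
- n = 2·((1.960 + 0.842)/h)² = 60 per arm, rounded up
- 60/(1 − 0.10) = 66.7, so 67, which matches.

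Other common formulas give 64 (72 after loss, pooled variance) or 62 (69 after loss, unpooled). The point about safety does not depend on which was used.

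**Plausible number of events.** 67 × 0.05 = 3.4 and 67 × 0.15 = 10.1, so roughly 3 to 10 infections per arm if the background rate applies.

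**Effect of exclusions.** The number of per-protocol exclusions is not given. I assume 7 of 67, which equals the planned loss in size (67 × 0.10 = 6.7) and leaves 60. With E events in all 67 and k of them among the 7 excluded:

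- all-treated rate = E/67
- per-protocol rate = (E − k)/60

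| E | All treated | k = 0 | k = 1 | k = 2 | k = 3 | k = 5 |
|---|---|---|---|---|---|---|
| 3 | 4.5% | 5.0% | 3.3% | 1.7% | 0.0% | – |
| 7 | 10.4% | 11.7% | 10.0% | 8.3% | 6.7% | 3.3% |
| 10 | 14.9% | 16.7% | 15.0% | 13.3% | 11.7% | 8.3% |

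**When the rate is understated.** (E − k)/60 is below E/67 exactly when k/7 exceeds E/67, that is, when events are more frequent among the excluded than in the arm as a whole. For E = 7 the threshold is 7 × 7/67 = 0.73, so one excluded event is enough. For E = 10 it is 7 × 10/67 = 1.04, so two are needed. With no event among the excluded, the per-protocol rate is slightly too high.

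The table concerns one arm. The difference between arms also depends on how exclusions and events fall in the control arm, on which the document gives nothing.

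**The case against.** The strongest reply is that the per-protocol set is undefined and that analysis sets are often defined in a statistical analysis plan, which is not shown. Being excluded from the study under {11b} is not stated to mean removal from the safety set. With a single application in theatre, per protocol might loosely mean by treatment received. Criterion (c) may mostly concern visits and ultrasound, and a patient with a wound infection does not obviously meet it. Harms are still captured under {18a} and {22}. Emergency visits, readmission and lymphoedema are secondary endpoints and so fall under intention to treat. Patients are blinded, which makes withdrawal that differs by arm less likely.

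Much of this stands as a limit on what can be claimed. A reader might infer any of the following, and the document supports none of them:

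- **That the plan certainly understates risk, or biases the comparison towards no difference.** This needs excess events among the excluded and, for the comparison, a particular pattern across arms.
- **That the excluded are the patients most likely to have an infection or wound failure.** The criteria allow a link to complications but do not show one.
- **That readmission is affected in the same way.** It is a secondary endpoint, not a main safety measure.
- **That the exclusions could plausibly hold every event.** With 3 events, 0 of 60 would remain, and the exact two-sided 95% upper limit would be 1 − 0.025^(1/60) = 6.0%. If exclusion were unrelated to events, the chance of this is (7×6×5)/(67×66×65) = 0.07%. It is a boundary, not a forecast.
- **That the 10% loss to follow-up is the per-protocol exclusion rate.** It is a different quantity, and events after a patient is lost are unseen in any analysis set.

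The reply does not remove the point. The article states the population for safety; it does not leave it open. A by-treatment-received meaning is not in the text, and stating it would call for the same correction. Intention to treat for some secondary endpoints does not cover adverse events, suture failure and wound infection. Capturing harms does not help the comparison if the patients are then left out of it.

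**Conclusion.** The point holds in this form: the plan fixes a per-protocol population for a main objective, with no analysis of all treated patients, where exposure is complete at surgery and exclusion can follow from a complication. The result may understate risk.

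Understatement is the expected direction, not a certainty. The actual size cannot be computed, because the document gives neither safety rates by arm nor a definition of the set. The calculation shows only sensitivity: under the assumed 7 exclusions and 7 events among 67 sealant patients, a true 10.4% could be reported as anything from 11.7% (no excluded events) to 3.3% (five excluded events).

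The primary efficacy analysis and the sample size are not affected.

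**What to change.** Replace the safety sentence in {20a} with text to this effect:

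*Safety (adverse events, suture failure, surgical wound infection) will be analysed in all randomised patients who had the lymphadenectomy, grouped by whether sealant was actually applied. No patient will be left out for missed visits, eligibility or later withdrawal, and events will be counted up to the last contact.*

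Keep a per-protocol analysis at most as a sensitivity analysis, with its set defined in advance. Add a clause to {20c} so that the removal of ineligible patients does not apply to safety.

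The cost is one replaced sentence and that clause. No new data are needed, since {18a} already requires forms for non-completers and {22} the recording of all adverse events. The sample size stays at 67 per arm.

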### Interim analyses {21b}

No interim analysis is planned in the current study.

### Methods for additional analyses (e.g., subgroup analyses) {20b}

Analyses of the primary and secondary outcome will be done in relation to subgrouping variables including age, sex, type of tumor, neoadjuvant treatment, and pathological history.

For each subgroup analysis, we will undertake a Cox proportional hazards model assessing each primary outcome incorporating a subgroup interaction term to provide the basis for evaluating subgroup effects. We will consider the possibility that a subgroup effect is present if the interaction term of treatment and subgroup is statistically significant at a *p*-value < 0.05. We will also consider other credibility criteria to judge the reliability of a subgroup effect.

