## Outcomes {12}

### Primary outcome

Percentage of patients with symptomatic seroma, defined as a seroma requiring its puncture-aspiration.

Seroma puncture-aspiration is indicated in the following scenarios during follow-up:Tension seroma causing uncontrollable pain (VAS = 5) even though taking the recommended oral analgesia (paracetamol 1 g/8 h alternating with metamizole 575 mg/8 h)Seroma volume not allowing a full adduction of the upper limb and causing discomfort as a result

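### The subgroup section tests the yes/no primary outcome with a Cox model, although the plan's effect measure is an odds ratio from logistic regression

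*Protocol article*

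**What the plan says.** All places are in the protocol article.

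- **Primary outcome** (Outcomes {12}): "Percentage of patients with symptomatic seroma, defined as a seroma requiring its puncture-aspiration". Only one primary outcome is listed, and each patient either has it or does not.
- **Sample size {14}:** the trial is sized on two percentages, 25% in the control arm and 7% in the sealant arm, giving 67 per arm.
- **Statistical methods {20a}:** "For the analysis of qualitative variables, the chi square test or Fisher’s test will be used as appropriate", and "The OR (odds ratio) is considered as a measure of effect calculated by logistic regression". Cox regression appears here under survival analysis, and the only survival outcome named is a secondary one: "Clinical lymphoedema-free survival will be analyzed using the Kaplan–Meier method".
- **Methods for additional analyses {20b}:** the primary and secondary outcomes are to be examined by "subgrouping variables including age, sex, type of tumor, neoadjuvant treatment, and pathological history". The section then fixes the model that will test whether the treatment effect varies across these variables: "we will undertake a Cox proportional hazards model assessing each primary outcome incorporating a subgroup interaction term". A subgroup effect is considered possible "if the interaction term of treatment and subgroup is statistically significant at a" p-value below 0.05, and further credibility criteria will also be weighed.

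**The concern.** The subgroup section names a model for time-to-event data and applies it to an outcome that the protocol defines, sizes and summarises as a proportion. It also speaks of the primary outcome as if there were several. The two main objectives (efficacy and safety) may explain that, but the Primary outcome section lists one.

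The question for the reader is comparability. The main result would be an odds ratio. The interaction would be a ratio of hazard ratios. An interaction that is null on one scale need not be null on the other when the baseline risk differs between subgroups, so a subgroup result could not be read directly against the overall effect. An analyst following the text would also have to build a time-to-aspiration variable that the protocol does not define.

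**Working it through.** **1. Is the trial designed around a proportion?** Inputs from Sample size {14}: 25% and 7%, two-sided alpha 0.05, power 0.80, 10% loss. The arcsine formula for two proportions gives

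- h = 2·asin(√0.25) − 2·asin(√0.07) = 0.512
- n = 2(1.960 + 0.842)² / h² = 59.96, so 60 per arm
- 60 / (1 − 0.10) = 66.7, so 67 per arm

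This reproduces the stated 67. The design calculation is for a yes/no outcome and uses no hazard.

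**2. How far apart are the two scales at the planning rates?**

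- Odds ratio = (0.07/0.93) / (0.25/0.75) = 0.226
- Hazard ratio under proportional hazards = ln(0.93) / ln(0.75) = 0.252

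**3. Do the two interaction nulls differ?** Assume a constant odds ratio of 0.226, so that there is no interaction on the logistic scale, and vary the control-arm risk by subgroup. The protocol gives no subgroup risks, so 10% to 50% is an assumed range. The treated risk p₁ follows from the odds ratio, and HR = ln(1 − p₁) / ln(1 − p₀).

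| Control risk p₀ (assumed) | p₁ at OR 0.226 | Implied HR |
|---|---|---|
| 10% | 2.45% | 0.235 |
| 25% | 7.00% | 0.252 |
| 40% | 13.08% | 0.275 |
| 50% | 18.42% | 0.294 |

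The ratio of hazard ratios between the 50% and 10% subgroups is 0.294 / 0.235 = 1.25. A Cox interaction would therefore target a non-null value where the odds ratio shows none.

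**4. How much information is there on an interaction?**

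- Expected events at 67 per arm: 67 × 0.25 + 67 × 0.07 = 16.8 + 4.7 = 21.4
- Expected events at 60 per arm: 60 × 0.25 + 60 × 0.07 = 15.0 + 4.2 = 19.2
- Standard error of the log ratio of odds ratios, with two equal subgroups (33.5 per arm in each): √{2[1/(33.5 × 0.25 × 0.75) + 1/(33.5 × 0.07 × 0.93)]} = 1.11
- Power for an interaction as large as the main effect: Φ(|ln 0.226| / 1.11 − 1.96) = about 27%

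The discrepancy in step 3 is ln 1.25 = 0.22, about a fifth of that standard error.

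**5. Chance findings.** The named variables are five: age, sex, type of tumour, neoadjuvant treatment and pathological history. With one primary outcome that makes five interaction tests.

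- Expected false positives: 5 × 0.05 = 0.25
- Probability of at least one, if independent: 1 − 0.95⁵ = 0.23

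**The case against.** The case for leaving the text alone has four parts.

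- **Cox is not impossible here.** Aspiration is an event that can be dated, and some loss to follow-up is expected. The time origin and censoring rule could sit in an analysis plan that is not shown. This is fair, and the point does not rest on those missing details. It rests on the stated model not matching the stated endpoint and effect measure.
- **The practical difference is tiny.** This stands. In simulated trials of 67 per arm with two equal subgroups and a constant odds ratio of 0.226, logistic and Cox interaction tests reached the same decision in about 99% of datasets, and Cox did not produce more false positives. That simulation assumed all aspirations fell on days 7, 14 or 30, and it left out datasets with an empty event cell, which are a sparse-data problem for either model.
- **The section has safeguards.** It treats a significant interaction only as a possibility and adds credibility criteria. A reader might infer that chance findings are likely to be reported as subgroup effects. The text does not support that.
- **The interaction rule is narrow.** A reader might count five variables by eight listed outcomes, giving 40 tests and an 87% chance of a false positive, or object that Cox cannot be fitted to pain, volume or quality of life. But the Cox sentence and its 0.05 rule cover only the primary outcome. Secondary outcomes appear only in the general opening sentence, with no model attached, so five tests is the supported count.

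A reader might also infer that hazard ratios would mainly reflect the day 7, 14 and 30 visits. Participant timeline {13} allows visits outside the schedule at the surgeon's discretion, and both arms follow the same assessments, so this is not established.

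**Conclusion.** The inconsistency is real and minor. The subgroup section prescribes a hazard model for a single binary outcome whose effect is otherwise expressed as an odds ratio. The text contradicts itself here, so this is more than a detail left to the analysis plan.

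The numerical consequence is small: 0.226 against 0.252 at the planning rates, and a spurious interaction ratio of about 1.25 over an assumed control-risk range of 10% to 50%, against a standard error of about 1.1 on the log scale. These figures rest on the planning rates, proportional hazards and two equal subgroups. The 23% chance of at least one false positive assumes five independent tests. The expected 19 to 21 events make any subgroup result exploratory whichever model is used. The primary treatment comparison and the sample size are untouched.

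**What to change.** In Methods for additional analyses {20b}:

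- Replace the Cox model by logistic regression for symptomatic seroma with treatment, subgroup and their interaction.
- Report the ratio of odds ratios with its confidence interval for each of the five variables, and label these analyses exploratory, citing the small number of events.
- Refer to the primary outcome in the singular.
- Keep Cox regression for lymphoedema-free survival, as Statistical methods {20a} already has it.

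If the investigators do intend a time-to-event analysis of the primary outcome, they should instead define time to first aspiration, with its origin and censoring rules, and explain how it relates to the odds ratio.

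The logistic route costs one paragraph of wording, needs no new data and leaves the sample size as it is. It should be settled before the database is locked.

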### Methods in analysis to handle protocol non-adherence and any statistical methods to handle missing data {20c}

Patients who are included in the study but who do not meet the inclusion or exclusion criteria will be withdrawn from the analysis. Missing data will be excluded for the primary and secondary outcome analyses. Further analyses based on multiple imputation methods will be considered if appropriate. Analyses will be carried out based on the intention to treat principle.

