### Trial design {8}

This is a multicenter, international, prospective, double-arm randomized clinical trial with a superiority design. Baseline data will be measured prior to randomization. Follow-up data will be collected at 7, 14, and 30 days after randomization. Long follow-up data will be collected at 6 and 12 months. A CONSORT diagram is presented in Fig. 1.

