### Participant timeline {13}

After surgery, all patients in the study will follow the same clinical assessments, which will be at days 7, 14, and 30 post-surgery. Patients will also be evaluated in the long term, at 6 and 12 months after surgery (Table 1). Clinical visits outside those that are established will be made at the discretion of the surgeon at each participating center.

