### Sample size {14}

Accepting an alpha risk of 0.05 and a beta risk of 0.2 in a bilateral contrast, 67 subjects in each study arm are required to detect a statistically significant difference in the percentage of patients with symptomatic seroma (which is expected to be 25% for the control group and 7% for the study group). A loss to follow-up rate of 10% has been estimated.

For the calculation of “*n*” and due to the large extent of seroma described in the literature, reference values of 25% described in the study by Jan et al. [9] have been taken.

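### The analysis is called intention to treat, but the same section removes randomised patients found ineligible and excludes missing outcomes, with no safeguard on who is removed or how

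*Protocol article*

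**What the plan says.** **Analysis principle.** Section {20a} of the protocol article says: "The statistical analysis plan (SAP) will be based on intention to treat principles". Section {20c} repeats the commitment.

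**Analysis set.** The same section {20c} says: "Patients who are included in the study but who do not meet the inclusion or exclusion criteria will be withdrawn from the analysis".

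**Missing outcomes.** It continues: "Missing data will be excluded for the primary and secondary outcome analyses". The sentence after that mentions multiple imputation, but only as a further analysis to be thought about if it seems suitable.

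**Withdrawal.** Section {11b} says "patients will be excluded from the study in any of the following scenarios". The scenarios are the patient's wish to leave, inability to complete the clinical controls, possible harm from continuing, and concurrent illness. Section {18a} adds that a case report form is completed even for patients who do not finish follow-up.

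**Who knows what, and when.** Under section {16c}, REDCap randomises once the inclusion criteria are met, and the surgeon knows the arm. Under section {19}, the surgeon in charge enters the eCRF data. Section {17a} blinds patients, statisticians and postoperative nurses.

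**The concern.** Intention to treat means that everyone randomised is compared in the arm to which they were allocated. The first rule in {20c} takes some of those patients out. The second takes out anyone whose outcome was not recorded. Both sit beside the claim that the analysis is by intention to treat, so an analyst cannot follow the section as written.

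The removal rule is open-ended. Eligibility is checked before the program allocates, so a patient removed for ineligibility is removed after allocation. Had the rule been confined to facts already true at randomisation and judged by someone blind to arm, it could have been harmless. No section sets such a limit. One exclusion criterion, the need for mastectomy, could plausibly come to light later, and the person who enters the data knows the arm.

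At stake is the primary comparison of a superiority trial. Its estimate could be shifted by who is removed, while the report presents it as protected by randomisation.

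**Working it through.** **1. The two statements side by side.** {20a} and {20c} promise intention to treat. {20c} also removes randomised patients on eligibility and drops missing outcomes. Both cannot describe one analysis set.

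**2. The plan's own sample size.** Section {14} says: "Accepting an alpha risk of 0.05 and a beta risk of 0.2 in a bilateral contrast, 67 subjects in each study arm are required", with symptomatic seroma "which is expected to be 25% for the control group and 7% for the study group" and a 10% loss to follow-up. By the arcsine formula:

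- h = 2·asin(√0.25) − 2·asin(√0.07) = 0.5117
- n = 2(1.960 + 0.842)² / h² = 59.96, so 60 per arm
- 60 / (1 − 0.10) = 66.7, so 67 per arm

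The stated 67 reproduces and already contains the 10% allowance. That allowance replaces lost numbers. It does not correct bias, and it covers loss to follow-up only, not removals for ineligibility.

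**3. How far unobserved outcomes could move the result.** Assumptions: 67 × 0.10 = 6.7, so 7 lost per arm, and observed counts near the planning rates, 15/60 vs 4/60. For two arms of n patients with a and b events and m = a + b, the uncorrected chi-square is 2n(a − b)² / [m(2n − m)].

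| Assumed events among the 7 lost (control, sealant) | Control vs sealant | Chi-square | p |
|---|---|---|---|
| Complete case | 15/60 vs 4/60 | 120·121/(19·101) = 7.57 | 0.006 |
| 7, 0 | 22/67 vs 4/67 | 134·324/(26·108) = 15.46 | < 0.001 |
| 3, 3 | 18/67 vs 7/67 | 134·121/(25·109) = 5.95 | 0.015 |
| 7, 7 | 22/67 vs 11/67 | 134·121/(33·101) = 4.86 | 0.027 |
| 0, 3 | 15/67 vs 7/67 | 134·64/(22·112) = 3.48 | 0.062 |
| 2, 5 | 17/67 vs 9/67 | 134·64/(26·108) = 3.05 | 0.081 |
| 0, 7 | 15/67 vs 11/67 | 134·16/(26·108) = 0.76 | 0.38 |

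The same number of events in both lost groups leaves the result significant, even at 7 and 7. Significance goes only when the lost sealant patients have clearly more events than the lost controls.

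**4. What this does not measure.** The table concerns missing outcomes. The documents give no figure for the number found ineligible. As an assumed range, removing a further 5% to 10% of 60 leaves 57 to 54 per arm. Power by the arcsine formula, Φ(h√(n/2) − 1.96), then falls from 80% at 60 per arm to about 78% and 76%. The loss of power is small; the bias cannot be computed.

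**The case against.** Several points on the other side are fair.

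- **Withdrawn patients.** A reader might infer that withdrawn patients are dropped by a stated analysis rule. The documents do not say that. {11b} excludes them from the study, under a heading on discontinuation, and {18a} keeps a form for non-completers. What remains is ambiguity: no section says whether a puncture recorded before withdrawal counts.
- **Per protocol.** A reader might call the efficacy analysis per protocol in disguise. No rule drops or moves efficacy patients for not receiving their allocated treatment. Per protocol is stated only for safety.
- **The surgeon as judge.** It is tempting to say that the unblinded surgeon decides who is ineligible later. {20c} does not name the decision-maker, and the statisticians are blinded. The supportable point is that neither the decider nor the timing is fixed.
- **One-sided scenarios.** Quoting only p = 0.062 and p = 0.38 would suggest a fragile result. Those cases give events to lost sealant patients and none to lost controls, and nothing in the documents supports that pattern.
- **Loss to follow-up.** Outcomes lost in this way are unobserved under any rule, and imputation detail is commonly left to the SAP, which is not shown. That is true, but the objection here is to rules that are printed and that conflict. An unseen SAP that followed {20c} would inherit them.

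**Conclusion.** The contradiction stands and concerns the primary estimate. As written, the plan yields a complete-case comparison of a reduced set under an intention-to-treat label. It is open to selection bias whose size and direction cannot be known from the documents.

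To say that randomisation is broken would go too far. The supportable statement is that the comparison is no longer of all patients as randomised, and that nothing stated guards against selective removal.

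The figures are bounds, not predictions. They rest on 7 of 67 lost per arm and on observed rates near those planned. Within them the full-set p-value runs from below 0.001 to 0.38, and the conclusion changes only under clearly differential loss. The sample size of 67 per arm is not in question.

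**What to change.** In section {20c}, and in the SAP to match:

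1. Replace the removal rule with a statement that all randomised patients are analysed in their allocated arm. At most, allow exclusion for ineligibility that was present before randomisation and is judged by someone blind to arm.
2. State that a puncture recorded before withdrawal counts as a primary event, and that data already collected on withdrawn patients are kept in the analysis.
3. Replace the optional wording on imputation with a commitment to two sensitivity analyses for missing primary outcomes: multiple imputation and a best/worst-case table like the one above. Whether imputation or complete case is the primary handling is a choice for the trial team, provided that it is named in advance.

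This needs no extra patients and no change to visits, and {18a} already provides for forms on non-completers. The cost is wording and a little more analysis. A change to the protocol text also goes through the ethics and registry steps in sections {23} and {25}. It should be settled before database lock.
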